**Severe**
“When you are *physically unable* to treat your hypoglycemia by yourself, it is considered a *Severe Hypoglycemia* event. You may be severely disorientated, unable to swallow, or unconscious. As a result, you are likely to need the help of another person to recover. This person may need to administer glucagon or a glucose injection to treat your severe hypoglycemia event. Emergency medical services may be called, and hospitalization may be required. Severe events can arise when your low blood glucose is left untreated and continues to drop. The early signs and symptoms of severe hypoglycemia typically include blurred vision, difficulty concentrating, confused thinking, slurred speech, numbness, and/or drowsiness. If your blood glucose stays low for too long, it can result in seizures, comas, and in rare cases, death. Consequently, severe hypoglycemia is a medical emergency.”
**Mild/moderate (also known as nonsevere)**
“When you are *physically able* to treat your hypoglycemia by yourself, it is considered a *Mild/Moderate Hypoglycemia* event. Treatment can include taking a glucose or sucrose tablet, drinking a glass of juice, or eating some food. Mild/moderate hypoglycemia events can be identified by symptoms such as shakiness, sweatiness or chills, irritability, feeling nervous or anxious, hunger, weakness, mild confusion, forgetfulness, fast heartbeat, feeling dizzy, and color draining from the skin. Mild/moderate hypoglycemia events can be identified from these symptoms or by a measured blood glucose level taken from a self-monitoring blood glucose (SMBG) meter or continuous/real-time glucose monitoring (CGM) device. You are still conscious and able to swallow.”
**Daytime**
“*Daytime events* (mild/moderate or severe) occur while you are awake.”
**Nocturnal**
“*Nocturnal events* (mild/moderate or severe) occur while you are sleeping or attempting to sleep. In addition to the symptoms described above, nocturnal hypoglycemia can be marked by symptoms such as vivid dreams/nightmares, restless sleep, morning headaches, night sweats, tiredness, irritability/confusion upon waking, convulsions, and talking/shouting while sleeping.”

### Ethical Considerations

iNPHORM was funded by an investigator-initiated grant from Sanofi Global (contract executed with Sanofi Canada, April 11, 2019). Before recruitment, we obtained ethics approval from the Western University health sciences research ethics board (December 17, 2019) and registered the study with ClinicalTrials.gov (NCT04219514; January 7, 2020). The COVID-19 subquestionnaire was approved as an ethics amendment before fielding.

A letter of information was emailed to all eligible respondents (Multimedia Appendices 5 and 6). The letter named Western University as the responsible academic institution and Sanofi Canada as the funding agency. It also outlined the study’s purpose, nature and expectations of participation (eg, content of surveys, time commitment, follow-up frequency, and incentivization), risks and benefits, participant rights (eg, refusals/withdrawals), and confidentiality/privacy measures (eg, data storage, retention, sharing, and reporting). Contacts were provided for IIS, faculty coprincipal investigator ([name]), Western University research team, and the Office of Human Research Ethics at Western University. Conflicts of interest for [name] have been declared. Consent was obtained via the web. Individuals were advised to read the letter of information before clicking on *I agree to participate* or *I do not agree to participate*.

Participation was voluntary. Enrollees could withdraw at any time by informing the IIS interviewer (pilot participants only), clicking an unsubscribe button provided in each email, or by emailing IIS directly. Privacy breaches and technical problems were monitored by IIS. Personally identifiable data (eg, phone numbers [pilot participants only], email addresses, and full birthdates) were encrypted automatically by the IIS platform and kept confidential from IIS and research personnel. IIS transferred deidentified data files to the Western University research team using a secure file transfer protocol on a password-protected network drive. All deidentified data will be stored for 7 years on a password-protected network drive at the Department of Family Medicine at Western University and on encrypted password-protected external drives; storage devices will be erased after this time. The iNPHORM assessments and data are owned by Western University.

Complying with US Food and Drug Administration postmarket safety reporting regulations [68], we emailed Sanofi United States and Novo Nordisk United States monthly pharmacovigilance reports of severe adverse events among Toujeo and Tresiba users, respectively. The reports were anonymized.

### Planned Statistical Analyses

#### Overview

Unique IDs, randomly assigned by IIS at the study outset, were used to tether the participants’ data across waves. Closed-ended responses were directly precoded, and a data dictionary and map have been developed. Repair rules addressing impossible, implausible, and discordant values will be documented in iNPHORM’s metadata (eg, erroneous responses will be classified as missing or cross-checked against valid responses). Both the raw and repaired data sets will be retained.

#### Describing the iNPHORM Sample

##### Recruitment and Completion Rate

The recruitment rate will be calculated as the ratio of consenting individuals to enrollees. The average total completion rates for the *iNPHORM longitudinal panel* will be computed as the ratio of the observed number of completed waves to the maximum expected number (12 waves per participant). To evaluate the success of our completion rate against our predetermined sample size (N=521; *Sample Size* section), the observed number of waves for which severe hypoglycemia information was available will be compared against the maximum expected number of completed follow-ups.

##### Completeness Rate

All data were stored in real time for analysis, even if the questionnaire was incomplete (eg, prematurely terminated). The completeness rate will be assessed after data cleaning and repair. Missing values will be coded as unit, block, item (because of skip logic), or residual (because of *not applicable*/*prefer not to say*/*I don’t know* or opt out) nonresponses. Missing data will be handled using multiple imputation by chained equations [69].

##### Participant Characteristics

Categorical variables will be summarized as frequencies and percentages, and continuous variables as means and SDs (parametric) or medians and IQRs (nonparametric).

#### Hypoglycemia Incidence (Coprimary Objective 1)

Crude severe and nonsevere daytime and nocturnal hypoglycemia incidence proportions and densities with 95% CIs for overdispersed count data will be reported overall and by diabetes type, medication regimen, mode of detection (symptoms and/or blood glucose), symptom severity (unconsciousness), and health care use. Incidence density calculations will account for observation durations as an offset for zero-risk and/or unobserved periods.

#### Prognostic Model Construction (Coprimary Objective 2)

##### Overview

The following procedures comply with current guidelines [70,71] and the Transparent Reporting of a Multivariable Prediction Model for Individual Prognosis or Diagnosis statement [72,73]. Analyses will be performed on baseline respondents who submitted ≥1 follow-up questionnaire. To pre-empt statistical power loss and selection bias, all baseline and follow-up data on this cohort will be examined [74]. Iterative proportional fitting (raking) [38] to correct for nonresponse and unequal selection probability will be investigated.

##### Model Development

Prognostic models will be developed for severe, nonsevere daytime, and nonsevere nocturnal hypoglycemia. Daytime and nocturnal severe events will be combined, given their nonspecific relevance and to ensure sufficient precision. Severe hypoglycemia will be modeled over 1 year using the Andersen-Gill Cox proportional hazards regression for recurrent events [34]. Nonsevere daytime and nocturnal hypoglycemia will be modeled over 30 days using negative binomial regression. Observation duration will be included as an offset variable, and generalized estimating equations will account for within-person dependence.

Candidate prognostic factors will be selected a priori based on biological plausibility, previous literature, data quality, measurement reliability, and multicollinearity. Intrinsic, extrinsic, nonmodifiable, and modifiable predictors (including frequency of previous severe and nonsevere hypoglycemia) will be considered. To minimize overfitting [75,76] and improve parsimony, model parameters will be estimated using machine learning penalized regression with Lasso (least absolute shrinkage and selection operator) [77]. Regression splines and fractional polynomials will assess the potential for nonlinearity and nonmonotonicity [78]. Interaction and subgroup analyses will be performed where suggested by external evidence [2]; sensitivity analyses will test the robustness of the findings. Informative censoring will be explored using inverse probability of censoring weighted estimation [79,80].

##### Internal Validation

Bootstrapping will be used to determine the optimism-corrected performance of each final model [74,77,81]. Discrimination will be evaluated using receiver operating characteristic curves and c-statistics [82]. Calibration will be assessed visually (eg, via graphical plots) and quantified using the calibration slope, the Hosmer-Lemeshow goodness-of-fit test, and the Grønnesby and Borgan test for survival data [83-85].

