**Results:**

Recruitment and data collection occurred between February 2020 and March 2021 (ethics approval was obtained on December 17, 2019). A total of 1694 participants completed the baseline questionnaire, of whom 1206 (71.19%) were followed up for 12 months. Most follow-up waves (10,470/14,472, 72.35%) were completed, translating to a participation rate of 179% relative to our target sample size. Over 70.98% (856/1206) completed wave 12. Analyses of sample characteristics, quality metrics, and hypoglycemia incidence and prognostication are currently underway with published results anticipated by fall 2022.

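### The Hosmer-Lemeshow and Grønnesby-Borgan p-values planned for internal validation ignore the within-person dependence of the models and become anti-conservative when between-person heterogeneity is left unexplained

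*Protocol article*

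**What the plan says.** All references are to the protocol article.

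- **Model Development**, nonsevere events: "Nonsevere daytime and nocturnal hypoglycemia will be modeled over 30 days using negative binomial regression". Observation time enters as an offset, and "generalized estimating equations will account for within-person dependence".
- **Model Development**, severe events: "Severe hypoglycemia will be modeled over 1 year using the Andersen-Gill Cox proportional hazards regression for recurrent events".
- **Prognostic Model Construction, Overview**, cohort: "Analyses will be performed on baseline respondents who submitted ≥1 follow-up questionnaire". The same paragraph says that all of this cohort's baseline and follow-up data will be used.
- **Internal Validation**: "Bootstrapping will be used to determine the optimism-corrected performance of each final model". For discrimination, "Discrimination will be evaluated using receiver operating characteristic curves and c-statistics". Calibration is to be judged from plots and "quantified using the calibration slope, the Hosmer-Lemeshow goodness-of-fit test, and the Grønnesby and Borgan test for survival data".

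The Internal Validation section does not say how a count becomes the binary outcome that Hosmer-Lemeshow and ROC curves need. It also does not say how dependence between one person's records enters the validation statistics. It sets no significance level or acceptance rule for either test.

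**The concern.** The plan recognises within-person dependence when it fits the models, then names calibration tests whose usual reference distributions leave it out. Hosmer-Lemeshow compares observed and expected numbers in risk groups and scales each squared difference by a variance that assumes independent binary records. If one person contributes about 10 positively correlated records to the same or neighbouring risk groups, the true variance of the observed total is larger than the assumed one. The statistic is then too large even when every prediction is right. The same happens to Grønnesby-Borgan when people differ in event rate beyond what the predictors explain.

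Developing and internally validating these models is the second coprimary objective, and the models are meant to feed a clinic-based tool. A small p-value that reflects clustering rather than miscalibration could lead the team to recalibrate or discard a sound model, or to report poor calibration that is not there.

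**Working it through.** **1. Records per person.** The Completion Rate section and Table 1 give 1,206 panel members, of whom 193 completed baseline only. The prognostic cohort is 1,206 − 193 = 1,013. The abstract states: "Most follow-up waves (10,470/14,472, 72.35%) were completed". This reproduces: 1,206 × 12 = 14,472, and 10,470 / 14,472 = 72.35%. Records per person are 10,470 / 1,013 = 10.3.

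**2. Mechanism by hand.** With m records per person and within-person correlation ρ, the variance of a group total grows by about 1 + (m − 1)ρ. Hosmer-Lemeshow with 10 groups and predictions taken as given is referred to chi-square with 10 df (5% critical value 18.31). Take m = 10 and two illustrative correlations:

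- ρ = 0.05: inflation 1 + 9 × 0.05 = 1.45. The false rejection rate is P(χ²₁₀ > 18.31 / 1.45 = 12.63), about 25%.
- ρ = 0.20: inflation 1 + 9 × 0.20 = 2.80. The rate is P(χ²₁₀ > 18.31 / 2.80 = 6.54), about 77%.

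**3. Simulation, nonsevere models.** The article states no rejection rate, so there is no figure of its own to reproduce. The setting was 1,013 people, 10 waves each, a correctly calibrated model, deciles of risk and a nominal 5% level. Assumptions not in the article: log-risk SD 0.8, mean 1 or 3 events per 30 days, month-level overdispersion 0.5 wherever between-person variance is above zero, gamma between-person variance as shown, 600 replicates. False rejection rates:

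| Between-person variance | Binary test, any event per person-month | Count version, negative binomial variance, clustering ignored |
|---|---|---|
| 0 | 4% to 6% | 4% to 7% |
| 0.1 | 14% to 16% | 25% to 43% |
| 0.5 | 58% to 67% | 75% to 86% |
| 2 | 92% to 97% | 94% to 98% |

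The row for variance 0 covers month-level overdispersion of 0, 0.5 and 1. With one record per person, rejection was 3% to 9% over all scenarios.

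A second, separately built set of runs of the binary test gave 5% with no unexplained heterogeneity, 24% to 28% at 0.1, 69% to 85% at 0.5 and 95% to 99% at 2. With one row per person it gave 3% to 8%. Less month-level noise raises the correlation between a person's records, and a rerun without that noise moved the rates upward in the same way. Together the two sets give about 14% to 28%, 58% to 85%, and over 90%.

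**4. Simulation, severe model.** Grønnesby-Borgan was run as the score test for decile indicators in the Andersen-Gill model, with fitted slope and 1,000 replicates. Event rates and variances are assumed.

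| Severe events per person-year | No heterogeneity | Variance 0.5 | Variance 6 |
|---|---|---|---|
| 0.3 | 6% | 10% | 73% |
| 1 | 5% | 32% | 98% |
| 2.5 | 6% | 64% | 100% |

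The first column shows that recurrent events alone do not disturb the test. Unexplained differences between people do.

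**The case against.** The strongest reply has four parts.

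- **No rule makes a model fail.** The article sets no level and no consequence, and the tests sit beside plots and a calibration slope. This stands. Clustering does not invalidate the point estimates of the slope or the plots; they need clustered intervals.
- **The article may intend one binary record per person**, in which case Hosmer-Lemeshow is close to its nominal size. The wording does not exclude this. However, the plan uses all follow-up data and generalized estimating equations, which serve no purpose with one record each. Pooled person-waves are the more natural reading.
- **Prior hypoglycemia frequency is a candidate predictor** and should absorb some between-person heterogeneity. That is fair, and it is why the variance of 0.1 belongs in the range. Even there the binary test rejects at about three times its nominal rate or more.
- **The target for the c-statistics is nearly implied.** Horizons of 1 year and 30 days are fixed, so any event within the horizon is the obvious choice. This largely stands, and stating it is a clarification. Left to the analysis plan, it would be no fault.

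A reader might infer that the bootstrap is wrong because it refers to each final model, or that optimism will be understated. The text does not say that imputation, penalty tuning or spline choice is left out of each resample, or that person-waves are resampled, so neither inference is supported. Separate performance figures for type 1 and type 2 diabetes would be a preference, not a correction.

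**Conclusion.** The point stands in a limited form. Two named tests do not match the dependence structure of the models they are meant to check. On pooled person-waves, their p-values are anti-conservative whenever between-person heterogeneity remains unexplained. The binary Hosmer-Lemeshow error rate ranges from about 5% with no such heterogeneity to over 90% at a variance of 2. Where in that range the study falls cannot be settled from the article, which gives no event rate, dispersion or within-person correlation.

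Three stronger readings are tempting and not supported:

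- That a well-calibrated model would almost always fail. This needs strong heterogeneity, which is an assumption.
- That none of the planned measures fits. The calibration slope and plots do, and ROC curves and c-statistics are estimates, not tests that a calibrated model can fail.
- That Grønnesby-Borgan is unusable because events recur. It held 5% to 6% under recurrence without unexplained heterogeneity.

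**What to change.** In the Internal Validation section or the analysis plan:

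1. Drop the Hosmer-Lemeshow and Grønnesby-Borgan p-values, or compute them with a participant-clustered variance. A negative binomial variance alone is not enough: it restored 4% to 7% only where there was no between-person heterogeneity.
2. Report observed/expected event ratios, the calibration slope already planned and smoothed calibration plots, all with participant-clustered intervals.
3. State the target of each c-statistic and ROC curve: any nonsevere daytime event within 30 days, any nonsevere nocturnal event within 30 days, and any severe event within 1 year.
4. State that the bootstrap resamples participants, not person-waves.

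No new data are needed. The cost is a few sentences and computing time.

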##### Pragmatic Tool Creation

Models will be converted into a user-friendly, clinic-based tool to complement real-world practice. Back-end computations of patients’ prognostic factors will provide point-of-care assessments for 1-year severe and/or 30-day nonsevere daytime/nocturnal hypoglycemia. To aid interpretation, risk estimates will also be categorized (eg, low, moderate, high, and very high).

The tool will be streamlined for easy integration in clinicians’ existing electronic medical records (EMRs) and compatible with prepopulated EMRs and manually inputted data. A standalone internet application and paper-based nomogram will be developed for when EMR integration is not possible. Real-time imputation will be explored [86].

#### Treatment-Related Causes of Hypoglycemia (Secondary Objective)

Differential effects of antihyperglycemic regimens on hypoglycemia rates will be tested using causal analytic techniques (eg, directed acyclic graphs, parallel and serial mediation, and time-dependent confounding). The results may help in identifying new and useful associations that can improve model performance or otherwise real-world event detection and management [87].

## Results

### Overview

iNPHORM commenced in February 2020 and concluded in March 2021. No bugs, downtimes, privacy breaches, or other unexpected events were reported/detected. Herein, we present the recruitment and completion rates (Figure 3). Analyses of participant characteristics and hypoglycemia incidence and prognostication are currently underway, with published results anticipated by fall 2022. Future studies will investigate the distributions of participant discontinuance [35] and systematically report on quality metrics, including missing values and data cleaning statistics, follow-up completeness [88], degree of coverage/sampling bias, and process outcomes (eg, average time-to-completion).

**Figure 3 figure3:**
[figure not shown]
Recruitment and completion rates. iNPHORM: Investigating Novel Predictions of Hypoglycemia Occurrence Using Real-world Models.

### Recruitment Rate

From February 10 to February 25, 2020, 2339 individuals consented to participate in iNPHORM; of these individuals, 1257 (53.74%) completed all actions to enroll (ie, *subpanel A*). Individuals in *subpanel A* who failed to complete wave 1 were withdrawn (488/1257, 38.82%) and systematically refreshed with *subpanel B*. From April 7 to April 23, 3197 individuals consented, of whom 437 (13.67%) were enrolled. Thus, as of April 2020, 1206 participants comprised the *iNPHORM longitudinal panel*.

### Completion Rate

The average total completion rate across the *iNPHORM longitudinal panel* was 72.4% (Multimedia Appendix 7). Given our use of systematic refreshment, *subpanel A* exhibited a higher completion rate than *subpanel B* (89.8% vs 41.6%, respectively). Dropout was highest at wave 1, with completion rates stabilizing thereafter. Across respondents, 71.89% (867/1206) completed ≥8 follow-ups, with 55.22% (666/1206) completing all 12 (Table 1). We observed minimal loss to follow-up (ie, individuals who discontinued participation until the end of the study). Most (855/1206, 70.9%) completed wave 12 (Table 2). Compared with our target sample size (N=521), we calculated a completion rate of 179% (Multimedia Appendix 8).

**Table 1 table1:** Number of questionnaires completed overall and by diabetes type (N=1206).

Number of questionnaires completed^a^	Respondents, n (%)		
	Total	T1DM^b^ (n=194)	T2DM^c^ (n=1012)
Baseline only^d^	193 (16)	29 (14.9)	164 (16.2)
1-7	146 (12.1)	20 (10.2)	126 (12.5)
8-11	201 (16.7)	35 (18.2)	166 (16.4)
All 12	666 (55.2)	110 (56.7)	556 (54.9)

^a^Questionnaires completed could be nonconsecutive.

^b^T1DM: type 1 diabetes mellitus.

^c^T2DM: type 2 diabetes mellitus.

^d^Only *subpanel B* respondents; *subpanel A* respondents were removed upon wave 1 noncompletion.

**Table 2 table2:** Number of respondents lost to follow-up after each wave overall and by diabetes type (N=1206).

Wave^a^	Respondents lost to follow-up after each wave, n (%)		
	Total	T1DM^b^ (n=194)	T2DM^c^ (n=1012)
Baseline^d^	193 (16)	29 (14.9)	164 (16.2)
Wave 1	33 (2.7)	8 (4.1)	25 (2.5)
Wave 2	17 (1.4)	2 (1)	15 (1.5)
Wave 3	10 (0.8)	1 (0.5)	9 (0.9)
Wave 4	14 (1.2)	0 (0)	14 (1.4)
Wave 5	7 (0.6)	0 (0)	7 (0.7)
Wave 6	5 (0.4)	3 (1.6)	2 (0.2)
Wave 7	8 (0.7)	0 (0)	8 (0.8)
Wave 8	6 (0.5)	1 (0.5)	5 (0.5)
Wave 9	8 (0.7)	1 (0.5)	7 (0.7)
Wave 10	12 (1)	0 (0)	12 (1.2)
Wave 11	38 (3.2)	9 (4.6)	29 (2.9)
Wave 12^e^	855 (70.9)	140 (72.2)	715 (70.7)

^a^Last wave responded to; after this wave, the respondent was considered to be lost to follow-up.

^b^T1DM: type 1 diabetes mellitus.

^c^T2DM: type 2 diabetes mellitus.

^d^Only *subpanel B* respondents; *subpanel A* respondents were removed upon wave 1 noncompletion.

^e^No data were collected past wave 12.

